# An active break program (ACTIVA-MENTE) at elementary schools in Chile: study protocol for a pilot cluster randomized controlled trial

**DOI:** 10.3389/fpubh.2023.1243592

**Published:** 2024-01-08

**Keywords:** active break, school, children, physical activity, on-task behavior

## Abstract

**Background:**

Physical inactivity is prevalent in childhood. Schools can be an ideal context to promote the regular practice of physical activity since children spend there a large part of the day. In this sense, an emerging and current trend is active breaks at school. This article presents a study protocol that seeks to assess the feasibility and effectiveness of an intervention with active breaks (ACTIVA-MENTE program) in a school context on physical activity, on-task classroom behavior, and the physical activity enjoyment in schoolchildren.

**Methods:**

The protocol includes children aged 10 to 11 years. Two groups will be randomized (intervention and control groups). The intervention group will use the active break program, ACTIVA-MENTE, which consists of the application of a 4-min, 30-s video with moderate to vigorous-intensity physical activity. These breaks will be taken 6 times a day in the classes for 6 weeks. The total physical activity will be measured with accelerometers (Actigraph wGT3X-BT), the on-task behavior through the Direct Behavior Rating Scale and the level of enjoyment through the Physical Activity Enjoyment Scale.

**Discussion:**

Previous research reported that active breaks have positive results in physical activity levels. This study will be one of the few to design active breaks through videos without depending on the presence of a physical education teacher and it can also provide new findings on the effectiveness of an active break’s structure (e.g., types of exercises and intensity) on the indicated outcomes.

**Expected results:**

It is expected that the ACTIVA-MENTE program can be a suitable program for school settings, potentially increasing physical activity levels, and the commitment to the task, as well as be a pleasant moment for the students.

**Clinical trial registration:**

Clinicaltrials.gov, identifier NCT05403996.

## Introduction

1

The benefits of physical activity for the quality of life of children and adolescents are well established, since it reduces the risk of chronic diseases and the symptoms of depression and anxiety, as well as improves the physical fitness, cognitive function and self-esteem (1–3). Additionally, physical activity is associated with better academic performance (4, 5) and behavior during school tasks (6, 7). In spite of this, worldwide reports reveals that more than 80% of the child population does not reach the recommended levels of physical activity (8). Moreover, the rates of physical activity implementation are expected to be reduced as the child ages from the first years of elementary school (9), worsening the physical inactivity status during growth and development phase. Of note, increasing children’s level of physical activity, especially moderate to high intensity, has significant implications for health and for accomplishing school tasks (10).

The integration of physical activity into the school routine is a key aspect to reduce sedentary behaviors. Elementary schools can be ideal settings for physical activity in children due to the amount of time spent at school and, in addition, due to the safe place with education professionals, who can direct not only the physical activity practice, but also include educational content (11). However, assigning more time for physical activity during the daily school often conflicts with the curricular demands, hiding physical activities promotion policies. Therefore, to make physical activity a priority in the school context, efficient strategies are needed (12). In this regard, active breaks are considered an emerging and suitable trend for physical activity integration into educational settings, fitting with the curricular timetable by interspersing extended periods of sitting with brief bouts of physical activity (13). It has been reported that active breaks are effective for increase the level of physical activity, for improve the classroom behavior (on-task behavior) (14) and for the enjoyment of movement (15).

Several factors are associated with active breaks practical application. The evidence shows that the teachers’ perception of the use of active breaks is usually positive (12, 16). Notwithstanding, it must be short, fast, suitable to be performed in the limited space available in the classroom, easy to implement (without sophisticated technological equipment) and must not imply a great time responsibility related to the teachers’ academic load (16). Without these characteristics, active breaks could have an adverse effect particularly on classroom behavior (17).

Recent reviews (11, 15, 18) proposed three approaches to implementing active breaks: (1) Active breaks as an interval/rest between two successive lessons; (2) Active breaks taken during the lesson; (3) Physical activity classes, with physical activity integrated into other subjects (e.g., mathematics, history, etc.). These multiple alternatives has shown to be limited due to a very broad school curriculum and the established priority for standardized tests (19). In spite of these limitations, interventions with active breaks implemented by the classroom teacher, or even using basic technology (e.g., audio) (20, 21) with duration of 10 to 20 min, two or three times a week twice a day (22, 23), or from three to five minutes every day (19, 24), show effectiveness to improve the physical activity level, academic performance, enjoyment, desire to learn, concentration and on-task behavior. Therefore, physical activity included in the daily instruction does not detract from academic performance, but it may actually enhance it (18). As a result, the academic classroom has the potential to be an integral component of a whole-of-school approach to physical activity that provides multiple health and learning benefits. Hence, is necessary to study the active breaks interventions because these can be an interesting potentially strategy to promote physical activity attractiveness for the students and teachers (25). In this sense, this work contributes to the existing gap regarding the incorporation and implementation of physical activity interventions in the classroom and in this way to increase the physical activity level, on-task behavior and enjoyment, since, unlike many school-based physical activity interventions, activity breaks require minimal disruptions in lessons (26). It is noteworthy that, there is not a consensus regarding the type of intervention (exercises type, amount, frequency and duration) and therefore more experimental evidence’s is required that addresses different intervention strategies (11, 27).

## Aim

2

The aim of this study is to evaluate the effectiveness of an intervention with active breaks - ACTIVA-MENTE - on children’s physical activity levels, on-task classroom, and physical activity enjoyment.

## Materials and methods

3

### Study design

3.1

The study is carried under a quantitative method. This study uses an experimental design with a pre-and post-test. The sample will be divided into two groups: intervention and control. An active break program - ACTIVA-MENTE – will be applied to the intervention group in their respective classes during the school day for 6 weeks, while the control group will perform their regular school day (without any intervention).

The protocol was developed in agreement with Standard Protocol Items: Recommendations for Interventional Trials (SPIRIT) and according to the verification guidelines of Consolidated Standards of Reporting Trials (CONSORT). Figure 1 provides a general description of the chronogram of enrolment, interventions and assessments.

**Figure 1 fig1:**
[figure not shown]
Standard Protocol Items: Recommendations for Interventional Trials (SPIRIT) (28). −*t*_1_, enrolment of the school and participants; 0, allocation of the groups and baseline assessments (high, weight, age); *t*_1_–*t*_6_, Intervention active breaks; t_1_, t_3_, t_6_ assessments; t_7_, post assessments (high, weight, age).

### Study sample

3.2

The study will be conducted at elementary schools in Valparaíso, Chile, from a low to middle low socioeconomic level (C_3_-D, respectively) (29). This group was selected in attempt to get a representative sample, since most of the Chilean population are classified with these socioeconomical level (29). The study sample consists in students of 10 to 11 years of age. The students who attend these schools spend approximately 8 hours a day at school (from 8:00 a.m. to 4:00 p.m.) with two recesses of approximately 15 min each (30 min altogether) and a longer rest for lunch of between 45 min and 1 h. For reasons of viability, the intention is to recruit two schools (one for intervention and another for control), from which a total sample size of 60 students is estimated.

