### Sample size, recruitment, participants and allocation

3.3

Prior to starting the present study, a power analysis was performed (G*Power 3; Heinrich-Heine-Universität, Düsseldorf, Germany) to calculate the adequate sample size (F-test, effect size = 0.25, α error = 0.05, power = 0.95). According to this calculation, the participation of 54 students is estimated. Being an experimental study, the sample is not large, however it has great power and can be representative of this group of students (30).

The eligible school directors will be invited to participate initially by e-mail and then they will be contacted a week later by telephone. A researcher will meet with all the interested directors to explain the requirements for participation in the study. Then, be organized a presentation day to explain the project to the teachers and students. Those who agree in include their schools in the study will receive a statement in simple language and a consent form to be signed. The recruitment lasts 2 months and will be during the year 2024. Finally, the study setting is two primary school in the city of Valparaíso, Chile.

Once the consent of the school authorities has been obtained, the consent in writing for the elementary classroom teachers to participate will be obtained, since the intervention will be part of the daily class activities. Afterward, all the children in the participating courses will receive a document with the information regarding the program containing a declaration in simple language, a consent form for the parents or guardians, and an assent form confirm the children’s participation. After this authorization, the ACTIVA-MENTE program will be carried out with all the children in the classes, but only data from children which the parents’ consent and their assent of participation will be compiled. The participation in the program will be volunteer and if the children are free to decide to give in the program whenever they want.

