The randomization will be carried out by a blind researcher who has no contact with the schools or participants, using a random numerical sequence generated by the Oxford Minimization and Randomization (OxMaR) computer program (31). All the schools will be from areas of a middle socioeconomic position in a similar geographic location, avoiding great differences between the groups baseline characteristics (Figure 2). Possible differences identified between the intervention and the control groups will be adjusted in the statistical analyses to not influence the results.

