### Statistical analysis

3.10

All the statistical analyses will be performed using jamovi software (50). The data will be reported as the mean and standard deviation for both experimental and control groups. Multilevel mixed-effects linear regression models will be used to assess the impact of the group (intervention vs. control) on the average scores of the physical activity level, on-task behavior and enjoyment of physical activity during whole intervention. Each variable will be fit by baseline levels of the corresponding variable and grouping by classes. All the analyses will control for the levels of physical activity at the beginning. All the analyses will be stratified by sex. We will consider the results statistically significant only if the *p* value will be lower than 0.05. We will calculate the effect size to examine the magnitude of any mean differences.

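### With one school per arm, the program effect cannot be separated from a school effect, so the class-level model and the p<0.05 rule do not support a conclusion about effectiveness

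*Protocol article*

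**What the plan says.** The title describes the article as a "study protocol for a pilot cluster randomized controlled trial". Section 3.2 says that "the intention is to recruit two schools (one for intervention and another for control", with 60 students expected in total. Section 3.3 repeats that "the study setting is two primary school in the city of Valparaíso, Chile".

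Section 2 sets a single purpose: "The aim of this study is to evaluate the effectiveness of an intervention with active breaks". The abstract also names feasibility. Viability, fidelity and acceptability appear in Sections 3.6, 3.7.3 and 4, but not in Section 2.

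Section 3.3 sizes the study with "F-test, effect size = 0.25, α error = 0.05, power = 0.95" and concludes that "the participation of 54 students is estimated". It gives no ICC or design effect. On imbalance it states: "Possible differences identified between the intervention and the control groups will be adjusted in the statistical analyses to not influence the results".

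Section 3.10 plans multilevel linear models for the group effect, with this structure: "Each variable will be fit by baseline levels of the corresponding variable and grouping by classes". A result counts as significant if p is below 0.05. School is not named as a level. The only limitation in Section 5 is that the study is not designed for adolescents.

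**The concern.** Randomising two schools decides which one receives the program. It does not balance school characteristics, because each arm holds one school. Anything that makes the two schools differ in the outcome enters the estimated program effect in full.

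The two stated safeguards do not reach this. Grouping by class captures variation among classes within a school, not between schools. Covariate adjustment can handle measured child characteristics, but a school effect occupies the same column as arm and cannot be fitted beside it.

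The risk is that the 0.05 rule labels a school difference as a program effect, in a report whose stated aim is effectiveness and which nowhere mentions the problem.

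**Working it through.** **Inputs.** From the protocol article: one school per arm (3.2, 3.3), 60 students (3.2), f = 0.25, alpha 0.05, power 0.95 and N = 54 (3.3), class grouping and p<0.05 (3.10). Assumed, because the article does not give them: an equal split (60/2 = 30 per school), a residual school ICC of 0 to 0.10, a class ICC of 0.03, and one to three classes per school.

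**1. The plan's own figure.** N = 54 is reproduced by a repeated-measures group-by-time interaction with two groups, m = 2 measurements and correlation 0.5 (both assumed):
- noncentrality = f² × N × m/(1 − rho) = 0.0625 × 54 × 2/0.5 = 13.5, with 1 and 52 degrees of freedom, giving power 0.9501.
- With the correlation kept at 0.5, three measurements give 44 and four give 36. A one-way F-test gives 210.

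The calculation that yields 54 treats pupils as independent. It has no school or class term.

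**2. Degrees of freedom between schools.** With k schools per arm these are 2(k − 1). For k = 1 this is 2(1 − 1) = 0, so no school-level standard error exists. This result needs no assumption about ICC, class count or split.

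**3. Pupil-level test.** This applies if each school has one class. The ICC then covers school and class together.
- Design effect = 1 + (30 − 1) × ICC = 2.45 at 0.05 and 3.90 at 0.10.
- Type I error = 2(1 − Φ(1.96/√DE)) = 0.210 and 0.321.
- A t test that uses the within-school variance inflates by 1 + 30 × ICC/(1 − ICC) = 2.58 and 4.33. On 58 degrees of freedom this gives 0.218 and 0.340.

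In this one-class case the class variance is also not identifiable. The standard error of the arm difference is √(2(v + 1/30)) in residual SD units: 0.26, 0.41 or 1.03 for v = 0, 0.05 or 0.5. The restricted likelihood (REML) does not distinguish between them.

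**4. Two or three classes per school.** The model has a class random intercept, class ICC 0.03, and a school variance that the model omits (200,000 simulated trials per setting):

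| Residual school ICC | Classes per school | Satterthwaite-type df | Wald z |
|---|---|---|---|
| 0 | 2 | 5.0% | 7.1% |
| 0 | 3 | 4.0% | 6.0% |
| 0.05 | 2 | 12.8% | 19.4% |
| 0.05 | 3 | 13.3% | 19.2% |
| 0.10 | 2 | 18.3% | 28.9% |
| 0.10 | 3 | 21.7% | 29.7% |

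A hand check of the mechanism uses a t test on class means, with two classes of 15 per school and school ICC 0.05. The variance of an arm mean that the test can see is (0.03 + 0.92/15)/2 = 0.0457. The true variance is larger by the factor 1 + 0.05/0.0457 = 2.09. The critical value 4.303 on 2 degrees of freedom becomes 4.303/√2.09 = 2.97, which gives an error of 9.7%. The mixed model is worse than this because it sometimes estimates the class variance as zero and then uses pupil-level degrees of freedom.

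**The case against.** **Pilot status.** Two schools are reasonable for a pilot, and much of the article concerns viability, fidelity and acceptability. That stands as a defence of the design. It does not defend Section 2 or the significance rule, which are confirmatory.

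**Baseline adjustment.** The relevant ICC is the one left after adjustment, and adjustment can reduce stable school differences. This is why the figures above are scenarios for a residual ICC. Adjustment cannot remove school-specific change over the six weeks. The help may also be uneven: Section 3.7.3 mentions accelerometry before the intervention, whereas on-task observation is placed only in weeks 1, 3 and 6.

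**Readings that go too far.** A reader might infer four stronger claims that the article does not support.
- That no valid p-value is possible. If residual school variance is zero, the error is near nominal. The difficulty is that this design cannot check that condition.
- That each school has a single class, so that the model cannot be estimated. The number of classes is not stated, and the wording on classes and courses is plural. The non-identifiable class variance in step 3 is therefore conditional.
- That the group on-task score is one rating per class. Section 3.7.3 has observation before and after a break in three separate weeks. The ratings are repeated, but the independent classes are few.
- That the adjustment sentence in Section 3.3 is wrong as a whole. Adjusting for measured baseline imbalance is legitimate. Only the assurance that differences will then not affect the results claims too much.

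**Unseen analysis plan.** The one-school-per-arm allocation, the class grouping, the 0.05 rule and the effectiveness aim are all stated in the article. They are not details left to another document.

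**Conclusion.** The point holds and should be corrected before the trial is analysed. That arm and school coincide, with 0 between-school degrees of freedom, follows from the text alone.

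The size of the error depends on assumptions that the article does not settle: 30 pupils per school, the residual ICC, the class ICC and the number of classes. At residual school ICCs of 0.05 and 0.10, the nominal 5% becomes about 21-22% and 32-34% for a pupil-level test. It becomes about 13% and 18-22% with two or three classes per school, a class random intercept and Satterthwaite-type degrees of freedom. At zero residual ICC the planned test is about right, but the trial cannot show that it is in that situation.

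**What to change.** Keep the two schools and change the text:

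- **Section 2:** make feasibility, with fidelity and acceptability, the primary aim. This matches the title, the abstract and Sections 3.6, 3.7.3 and 4.
- **Section 3.10:** remove p<0.05 as a rule for effectiveness. Report arm differences descriptively. Label any between-arm interval as excluding between-school variation, because an unlabelled interval has the same fault as the p-value. Report the class-level on-task score descriptively only.
- **Section 3.3:** limit the adjustment sentence to measured baseline child characteristics, and drop the assurance that differences will not influence the results.
- **Section 5:** add the confounding of school with arm as a limitation.

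The cost is wording and a weaker stated conclusion, with no extra schools or children.

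Keeping an effectiveness test would cost far more. For a standardised difference of 0.5 (f = 0.25), 30 pupils per school and 80% power, a school-level comparison needs about 4, 7 or 10 schools per arm at an ICC of 0.01, 0.05 or 0.10, before any gain from baseline adjustment. Randomising classes within both schools would break the confounding, but it changes the design, risks contamination and leaves few clusters. It is a trade-off for the investigators and not part of the required fix.

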#### Inclusion criteria

3.2.1

Students aged 10 to 11 years old belonging to sixth grade elementary.

#### Exclusion criteria

3.2.2

The excluded students will be those who present a class attendance below 90%, or students who present some health impediment when the active breaks are taken, or students with cognitive disability. These criteria are used since the effect of the intervention on the study variables (level of physical activity, behavior in the task and enjoyment) depends on the physical and psychological disposition for carrying out the active breaks of the students. Participants which match with exclusion criteria will be excluded only from the data analysis.

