#### Secondary outcome: physical activity enjoyment

3.7.3

The Physical Activity Enjoyment Scale (PACES) (42) will be individually applied to the participants. This is a scale that has reported good reliability in children (Cronbach’s alpha of 0.96) (43), and it has even been used in other studies with this population (44, 45). The questionnaire will be applied referring to “when I participate in the active breaks…”.

Physical activity: ActiGraph wGT3X-BT accelerometers and the ActiLife 6 software will be used to measure the children’s level of physical activity, since this device is proven to have the validity and reliability to measure the physical activity level objectively in this age group (38). The accelerometers will be used during the school day prior to the intervention, in weeks 1, 3 and 6, in both the intervention and control groups. The accelerometers will be handed out and collected from the child at school at the beginning and end of each school day.

The accelerometers will be placed at the beginning of every school day, since the device is programmed and activated by an internal clock from the software so that it begins to record for the established time. The accelerometers are placed using an elastic belt at the intersection of the right hip and waist (on the iliac crest), as this is the place next to the center of gravity (39). Data from the participants who do not fulfill what is requested for the recording (days and hours) will not be analyzed. A short duration epoch of 15 s will be used; because the pattern, more intermittent the children’s physical activity (46), frequency of 100 Hz. The classification of the daily level of physical activity will be: sedentary, light, moderate, vigorous and moderate-vigorous, established from counts per minute. The cut-off point used will be determined by Evenson’s equation for the ActiGraph wGT3X-BT, especially used for students’ task classroom behavior (47) (sedentary 0–100 counts^x^min^−1^, light 100–2,295 counts^x^min^−1^, moderate 2,296–4,012 counts^x^min^−1^, vigorous 4,013 counts^x^min^−1^).

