Another strength of this study protocol is the measurement of the physical activity level using accelerometers, which give an objective measurement of the level of physical activity, as well as intensity. In addition, the data related to intensity will be complemented by the use of a heart rate monitor that will only be used during the application of ACTIVA-MENTE to provide a precise control of the intensity of the program’s activities. Furthermore, the teachers’ records regarding the physical activity performed are also included in the analysis. Together, both evaluations provide a differential and complete analysis in comparison with some studies which only assessed the physical activity level from the teachers’ reports. On the other hand, the application of this protocol seeks to investigate the integration of active breaks during the school day and their pedagogical impact, especially regarding students’ on-task behavior and enjoyment (55). In this line, some studies (11, 56) suggest that future investigations must focus on a rational and strategic application of interventions to evaluate their impact and effectiveness in the pedagogical process. In this sense, it is relevant that active break programs, such as ACTIVA-MENTE, include an assessment of student enjoyment related to the physical activities performed, which is another strength of the ACTIVA-MENTE study. Finally, ACTIVA-MENTE is designed to offer all children living in a situation of disability the opportunity to participate in the activities appropriate to their age and ability (3). This aspect is important, since the evidence shows that these disabled students not only enjoy physical activity, but also benefits themselves with this daily practice (57, 58). Specifically, this study can provide evidence regarding aspects, that are still not clear in active breaks, such as duration, intensity, types of exercise and inclusive methodology in a school context (59). The results of this study can provide useful information on the implementation and structure of future research that aims to address the feasibility and acceptance of intervention with active breaks, this is necessary, since active breaks are an emerging strategy to increase the physical activity level at school context and that has not yet been deepened (60).

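### Children are removed from the analysis by rules with no fixed timing, one tied to an event that occurs only in the intervention school, so the only analysis set described is open to selection bias

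*Protocol article*

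**What the plan says.** All references are to the protocol article.

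- **Section 3.2.2 (Exclusion criteria)** names students "who present a class attendance below 90%, or students who present some health impediment when the active breaks are taken", and students with cognitive disability. The reason given is that the effect on all three outcomes depends on the child's physical and psychological readiness for the breaks. The section then states: "Participants which match with exclusion criteria will be excluded only from the data analysis".
- **Section 3.3** says that the whole class takes part in the programme and that data are collected only from children with parental consent and their own assent.
- **Section 3.1** gives the control group its ordinary school day, with no breaks. **Section 3.2** sets one school per arm: "the intention is to recruit two schools (one for intervention and another for control".
- **Section 3.7.3** adds a rule on accelerometer wear, which applies to both groups: "Data from the participants who do not fulfill what is requested for the recording (days and hours) will not be analyzed".
- **Section 3.10** plans multilevel mixed models adjusted for baseline, with grouping by class. It names no analysis set other than the one these rules leave.
- **Sample size:** section 3.3 gives the inputs "F-test, effect size = 0.25, α error = 0.05, power = 0.95" and concludes that "the participation of 54 students is estimated". Section 3.2 describes the two schools as those "from which a total sample size of 60 students is estimated". No loss rate is stated.

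**The concern.** Rules that remove children from the analysis, but not from the programme, are safe only if they rest on facts fixed before allocation and are applied alike in both arms. Neither condition is secured here.

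The health rule is worded around the moment at which a break is taken, and that moment exists in one school only. The attendance rule has no period. Counted over the six intervention weeks, attendance is observed after allocation and could be affected by it. The stated reason, readiness to do the breaks, is the reasoning of a per-protocol analysis. It is applied to the only analysis set described, in a trial whose stated aim (section 2) is effectiveness.

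At stake is whether the two groups compared are still the groups that were allocated. A larger sample would not repair a difference created in this way.

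**Working it through.** **1. The plan's own figure.** Inputs from section 3.3: F-test, f = 0.25, α = 0.05, power 0.95. From section 3.1: two groups, pre and post (m = 2). Assumed, because not stated: correlation ρ = 0.5 and sphericity 1.

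For the group-by-time interaction, λ = f²·N·m/(1 − ρ), with 1 and N − 2 degrees of freedom. At N = 54, λ = 0.0625 × 54 × 2/0.5 = 13.5 and power is 0.9501. So 54 is reproduced.

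The other models tried do not give 54. The interaction with 3 or 4 measurements needs 44 or 36. The between-group repeated-measures test with 2, 3 or 4 measurements needs 158, 142 or 132. A one-way F-test needs 210.

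**2. The margin.** 60 − 54 = 6 children, or 6/60 = 10%. Seven or more losses leave 53 or fewer. The loss rate is not given, so a range is shown. Power is from the model in step 1. The last column assumes that each of the 60 children is lost independently.

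| Assumed total loss | Children left | Power | Chance of fewer than 54 |
|---|---|---|---|
| 5% | 57 | 0.960 | 3% |
| 10% | 54 | 0.950 | 39% |
| 15% | 51 | 0.938 | 82% |
| 20% | 48 | 0.924 | 97% |
| 25% | 45 | 0.906 | over 99% |
| 30% | 42 | 0.885 | over 99% |

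With all 60 analysed, power is 0.968.

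**3. The attendance rule alone, if counted in the trial.** Assume 6 weeks × 5 days = 30 school days and independent absence with daily probability q. Attendance below 90% then means more than 3 days missed. P(Binomial(30, q) > 3) is 0.061, 0.103, 0.216 and 0.353 for q = 5%, 6%, 8% and 10%, which leaves about 56, 54, 47 and 39 of 60. Power is about 0.92 at 47 and 0.86 at 39. All four absence rates are assumptions.

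**4. Selection.** In one arm, let p be the share of children removed and δ the mean baseline-adjusted outcome of those retained minus that of those removed. The full-arm mean is the retained mean minus p·δ, so removal shifts the arm mean by p·δ. The shift in the difference between arms is

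p_I·δ_I − p_C·δ_C

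(I = intervention, C = control).

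- *Health rule as worded:* controls have no breaks, so p_C = 0 and the shift is p_I·δ_I. Nothing in the other arm offsets it.
- *Attendance rule:* it applies in both arms. The terms cancel only if p·δ is equal in the two schools. Counted before allocation, the rule is an ordinary baseline restriction. Counted in the trial, equality is not assured.
- *Cognitive disability:* a baseline trait that can be judged in both schools.
- *Wear rule:* accelerometers are worn in both groups, so it is not confined to one arm.

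The document gives none of the p or δ values, so neither the sign nor the size of the shift can be computed.

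**The case against.** A benign reading is available. The criteria sit under an eligibility heading, next to a baseline trait. Because whole classes take part, restricting exclusion to the analysis may mean only that an ineligible child joins the breaks and supplies no data. Attendance may refer to the record before the trial. The health wording may be loose English for a condition that prevents exercise, which could be judged in both schools. This is enough to rule out saying that the comparison *is* biased. It does not clear the text, which fixes neither the timing nor the equal application of the rules and gives a reason based on ability to do the breaks.

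A reader might infer more than the document supports:

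- **That the bias favours the programme, because less able or less willing children leave one arm only.** One-sided removal can be argued only for the health rule. No rule removes the unwilling: section 3.3 makes participation voluntary, and section 3.2.2 does not list stopping as an exclusion.
- **That the trial will miss its sample size.** The absence rates are assumed. Also, 54/0.9 = 60, so a 10% allowance may have been intended, though the text does not say so.
- **That the exclusions contradict the inclusion claim in the Discussion, "ACTIVA-MENTE is designed to offer all children living in a situation of disability the opportunity to participate in the activities".** That sentence promises participation, which sections 3.2.2 and 3.3 preserve. Section 3.5 speaks of motor, auditory and visual disability, and section 3.2.2 names none of these. At most, children with cognitive disability supply no data on inclusiveness.
- **That the wear rule is itself an error.** It is a data-validity rule, and its thresholds may stand in the full protocol.

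Finally, with one school per arm, school and treatment are already confounded, so these exclusions are not the only threat to the comparison. That is a separate issue and no reason to leave them as they are.

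**Conclusion.** The point holds as a defect in how the analysis set is defined. The health rule refers to an event that occurs only in the intervention school. The attendance rule has no period and is a post-allocation variable if counted in the trial. No as-allocated analysis stands beside the restricted one. The comparison is open to selection bias of unknown direction and size.

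The effect on sample size is real but minor: losses above 10% from all causes take the analysed number below 54, at a modest cost in power. The power figures rest on the 2 × 2 interaction model with an assumed correlation of 0.5 and, like the plan's own calculation, take no account of clustering.

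**What to change.** 1. In section 3.2.2, define the health, cognitive and any attendance exclusions from information recorded before allocation. State the attendance period, and apply the criteria identically in both schools.
2. Make the primary analysis all eligible consenting children in their allocated group, whatever their later attendance or participation in breaks. Use all valid accelerometer weeks in the planned mixed model, so that an incomplete week does not remove the child.
3. Keep the set restricted by in-trial attendance, health impediment and complete wear as a labelled sensitivity (per-protocol) analysis.
4. State the loss allowed for between 54 and the recruitment target. The target is 54/(1 − d): 60 at d = 10%, 64 at 15% and 68 at 20%.

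Items 1 to 3 cost some rewording and one extra analysis, and change no intervention, visit or measurement. The estimate may be smaller, because children who took little part in the breaks are included. Item 4 costs extra recruitment only if the allowance exceeds 10%.
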